## Abstract

**Background:**

Acute respiratory distress syndrome (ARDS) is a complex clinical diagnosis with various possible etiologies. One common feature, however, is pulmonary permeability edema, which leads to an increased alveolar diffusion pathway and, subsequently, impaired oxygenation and decarboxylation. A novel inhaled peptide agent (AP301, solnatide) was shown to markedly reduce pulmonary edema in animal models of ARDS and to be safe to administer to healthy humans in a Phase I clinical trial. Here, we present the protocol for a Phase IIB clinical trial investigating the safety and possible future efficacy endpoints in ARDS patients.

**Methods:**

This is a randomized, placebo-controlled, double-blind intervention study. Patients with moderate to severe ARDS in need of mechanical ventilation will be randomized to parallel groups receiving escalating doses of solnatide or placebo, respectively. Before advancing to a higher dose, a data safety monitoring board will investigate the data from previous patients for any indication of patient safety violations. The intervention (application of the investigational drug) takes places twice daily over the course of 7 days, ensued by a follow-up period of another 21 days.

**Discussion:**

The patients to be included in this trial will be severely sick and in need of mechanical ventilation. The amount of data to be collected upon screening and during the course of the intervention phase is substantial and the potential timeframe for inclusion of any given patient is short. However, when prepared properly, adherence to this protocol will make for the acquisition of reliable data. Particular diligence needs to be exercised with respect to informed consent, because eligible patients will most likely be comatose and/or deeply sedated at the time of inclusion.

**Trial registration:**

This trial was prospectively registered with the EU Clinical trials register (clinicaltrialsregister.eu). EudraCT Number: 2017-003855-47.

## Administrative information

The order of the items has been modified to group similar items (see http://www.equator-network.org/reporting-guidelines/spirit-2013-statement-defining-standard-protocol-items-for-clinical-trials/).

**Table Taba:** 

Title {1}	Safety and preliminary efficacy of sequential multiple ascending doses of solnatide to treat pulmonary permeability edema in patients with moderate-to-severe ARDS - a randomized, placebo-controlled, double-blind trial
Trial registration {2a and 2b}.	Primary Registry and trial identifying number: clinicaltrialsregister.eu ; EudraCT 2017-003855-47 Date of registration in primary registry: 2 February 2018 Secondary identifying numbers: not applicable Sources of monetary or material support: Apeptico Forschung und Entwicklung GmbH Primary sponsor: Apeptico Forschung und Entwicklung GmbH Secondary sponsor(s): not applicable Contact for public queries: Apeptico Forschung und Entwicklung [name]. [name] [name] [name] [contact] Contact for scientific queries: Apeptico Forschung und Entwicklung [name]. [name] [name] [name] [contact] Public title: Safety and preliminary efficacy of sequential multiple ascending doses of solnatide to treat pulmonary permeability edema in patients with moderate-to-severe ARDS - a randomized, placebo-controlled, double-blind trial Scientific title: Safety and preliminary efficacy of sequential multiple ascending doses of solnatide to treat pulmonary permeability edema in patients with moderate-to-severe ARDS - a randomized, placebo-controlled, double-blind trial Countries of recruitment: Austria, Germany Health conditions or problems studied: pulmonary permeability edema in patients with moderate-to-severe ARDS Interventions: Bronchial inhalation of ascending doses of solnatide vs. placebo for seven days Key inclusion and exclusion criteria: Ages eligible: ≥ 18 years Sexes eligible: both Accepts healthy volunteers: no Inclusion criteria: diagnosis of moderate to severe ARDS according to the Berlin definition, need for mechanical ventilation, pulmonary edema (EVLWI ≥10 ml/kg PBW), informed consent Exclusion criteria: allergy against solnatide, severe septic shock, extracorporeal membrane oxygenation at time of screening Study type: interventional allocation: randomized intervention model: parallel assignment masking: double blind (patient, caregiver, investigator, outcomes assessor) Date of first enrolment: 23.05.2018 Target sample size: 95 Recruitment status: ongoing Primary outcome: Safety (mortality, AEs, SAEs, laboratory data, ECG) Key secondary outcomes: extravascular lung water index (EVLWI), pulmonary vascular permeability index (PVPI), oxygenation ratio, ventilation parameters

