## Trial design {8}

This is a Phase IIb, randomized, placebo-controlled, double-blind, dose escalation study. The study will be conducted in up to 10 centers located in Germany and Austria. Additional European countries may be involved.

Thirty eligible patients with pulmonary permeability edema (EVLWI ≥ 10 ml/kg PBW) and moderate to severe ARDS admitted to an intensive care unit (ICU) and under mechanical ventilation will be randomized in a 2:1 ratio to receive either a low dose of solnatide (5 mg) (20 patients) or placebo (10 patients). Patients will be treated for up to 7 days and the study duration for each patient is of up to 28 days.

Following the end of the study period for these patients and prior to escalating from the low dose to the middle dose (60 mg), safety data collected during the 28-day study period will be reviewed by an independent Data Safety Monitoring Board (DSMB), who will decide whether the safety profile is acceptable for dose escalation. In case of positive outcome, 25 new patients will be randomized to solnatide 60 mg or placebo in a 4:1 ratio in order to have 20 patients randomized to the middle-dose group and 5 to the placebo group.

After the end of the study period of these patients and prior to escalating from the middle dose to the high dose (125 mg), safety data will again be reviewed by the DSMB, who will decide whether the safety profile is acceptable for escalating to the high dose.

If so, 40 new patients will be randomized to solnatide 125 mg and placebo in a 1:1 ratio in order to have 20 patients randomized to the high-dose group and 20 patients to the placebo group.

The randomization ratios solnatide/placebo (i.e. 2:1; 4:1; 1:1) will allow to have a total of 35 patients assigned to placebo. In addition, the randomisation schedule will provide the DSMB with enough placebo patients to perform the safety analysis.

To conduct the study, approximately 95 patients will therefore be randomized (see Fig. 1).

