### Sample size {14}

Given that the primary objective of the study is to investigate the safety of solnatide, the study sample size of 95 randomized patients is based on feasibility criteria.

Patients will be randomized to 3 groups of 20 patients each, representing the 3 multiple ascending dose groups receiving solnatide at doses of 5 mg, 60 mg and 125 mg, and 35 patients will receiving placebo in total, with 15 patients receiving placebo in Dosing Group A (low dose) and Dosing Group B (middle dose) and 20 patients receiving placebo in Dosing Group C (high dose).

Nevertheless, considering the key preliminary efficacy endpoint and the results of a Phase IIa study (2012-001863-64), a sample size of 20 evaluable patients in each treatment group will have approximately 80% power to detect a difference in means between solnatide and placebo of 3.2 ml/kg in the change from baseline to day 7 of EVLWI with a common SD of 3.5 using a two-group *t*-test with a 0.05 two-sided significance level and no alpha level adjustment for multiple testing.

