## Assignment of interventions: allocation

### Sequence generation {16a}, concealment mechanism {16b} and implementation {16c}

A randomization plan will be generated before study start. No stratification factors are planned. Three different randomization lists (one for each step of the study) will be prepared with the following randomization ratios:
2:1 in the first step of solnatide 5 mg vs. placebo4:1 in the second step of solnatide 60 mg vs. placebo4:1 in the third step of solnatide 125 mg vs. placebo

The randomization process will be managed electronically (block-wise generation of random numbers) by means of an Interactive Web Response System (IWRS) to ensure that treatment assignment is unbiased and concealed from patients and investigator staff. The results of the randomization are merely revealed to the responsible study pharmacist, who will then facilitate the preparation of the respective IMP. IMP vials are transferred to the investigators in a neutral container. Solnatide and placebo solutions cannot be distinguished from one another by the investigators.

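### The third randomisation list is specified as 4:1, which contradicts the 1:1 high-dose step on which the stated group sizes and placebo total depend

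*Protocol article*

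**What the plan says.** Trial design {8} of the protocol article sets out three sequential steps:

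- Step 1: patients are "randomized in a 2:1 ratio to receive either a low dose of solnatide (5 mg) (20 patients) or placebo (10 patients").
- Step 2: "25 new patients will be randomized to solnatide 60 mg or placebo in a 4:1 ratio", that is 20 active and 5 placebo.
- Step 3: "40 new patients will be randomized to solnatide 125 mg and placebo in a 1:1 ratio", that is 20 and 20.

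The same section ties the ratios to the placebo total: "The randomization ratios solnatide/placebo (i.e. 2:1; 4:1; 1:1) will allow to have a total of 35 patients assigned to placebo". It concludes that "approximately 95 patients will therefore be randomized". Sample size {14} agrees: three active groups of 20, 35 placebo in total, 15 of them in Dosing Groups A and B together, and "20 patients receiving placebo in Dosing Group C (high dose"). The registration table gives only the overall number, "Target sample size: 95".

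Sequence generation {16a} says that three lists will be prepared, one per step. The first is "2:1 in the first step of solnatide 5 mg vs. placebo" and the second is 4:1 for 60 mg, both as in {8}. The third is given as 4:1 for 125 mg against placebo. That entry conflicts with {8} and {14}.

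**The concern.** The lists in the web response system decide who receives what, so the section that specifies them is the operative one. If the third list were built as {16a} describes, the high-dose step would have far fewer placebo patients than {8} and {14} promise.

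This matters for three reasons:

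- Safety is the main objective, and {8} says the randomisation schedule is meant to give the DSMB enough placebo patients for its safety analysis.
- The steps run one after another, each waiting for the previous group's 28-day data. Placebo patients from steps 1 and 2 are therefore not concurrent with the 125 mg patients.
- The 125 mg comparison on EVLWI is tested first, and the lower doses are tested only if it succeeds.

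**Working it through.** **1. Reproduce the stated totals with the {8} ratios.**
Total: (20 + 10) + (20 + 5) + (20 + 20) = 30 + 25 + 40 = 95. Placebo: 10 + 5 + 20 = 35. Both match {8} and {14}.

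**2. Replace 1:1 by 4:1 in step 3, as in {16a}.**

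- (a) Keep 20 patients on 125 mg: placebo = 20/4 = 5, so step 3 has 25 patients. Total 30 + 25 + 25 = 80; placebo 10 + 5 + 5 = 20.
- (b) Keep 40 patients in step 3: placebo = 40/5 = 8 and active = 32. Total 30 + 25 + 40 = 95; placebo 10 + 5 + 8 = 23; 32 − 20 = 12 more patients on 125 mg than stated.
- (c) Keep 20 placebo patients in step 3: active = 4 × 20 = 80, so step 3 has 100 patients and the trial 30 + 25 + 100 = 155.

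**3. Can any split of 95 rescue the figures?**
With one 2:1 list and two 4:1 lists the placebo share cannot exceed 1/3, so placebo is at most 95/3 = 31.7, below 35. No split works.

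**4. Power for 125 mg against placebo.**
Inputs from {14}: difference 3.2 ml/kg in EVLWI change to day 7, SD 3.5, two-group t-test, two-sided 0.05. Power comes from the noncentral t distribution with df = n1 + n2 − 2 and noncentrality 3.2 / (3.5 × √(1/n1 + 1/n2)).

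The plan's own figure first: 20 vs 20 gives noncentrality 3.2 / (3.5 × 0.3162) = 2.89, df 38, power 80.4%. This reproduces the stated 80%.

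| Step 3 | Against step-3 placebo only | Against placebo pooled over steps |
|---|---|---|
| 1:1, as in {8} | 20 vs 20: 80.4% | 20 vs 35: 89.3% |
| 4:1, reading (a) | 20 vs 5: 41.8% | 20 vs 20: 80.4% |
| 4:1, reading (b) | 32 vs 8: 61.6% | 32 vs 23: 90.7% |

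Against step-3 placebo only, the difference detectable with 80% power rises from about 3.2 to 5.1 ml/kg in (a) and 4.0 ml/kg in (b).

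**5. How much of a pooled placebo group would be non-concurrent with the 125 mg patients?**
Steps 1 and 2 supply 15 placebo patients in every case. That is 15/35 = 43% as designed, 15/20 = 75% under (a), and 15/23 = 65% under (b).

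**The case against.** The strongest reply is that the intended ratio is not in doubt. Trial design {8} states 1:1 for step 3, repeats it in the string of three ratios and gives 20 and 20; {14} repeats 20 placebo in Group C. The 4:1 entry may simply duplicate the line above it. The article is not the list itself, and nothing in it shows that a 4:1 list was loaded. All of that stands. It explains how the error may have arisen, but it does not settle which version was implemented, and the section with the wrong figure is the one that specifies the lists.

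The reply also limits three inferences that a reader might draw:

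- *That the registered target of 95 is wrong or unreachable.* It is not. The registration table agrees with {8}, gives no placebo count, and 95 can still be reached at 4:1 as 32 and 8. What fails is the combination of 95 patients, 35 placebo and 20 per dose.
- *That the stated 80% power is lost.* This follows only if 125 mg is compared with step-3 placebo alone. The EVLWI analysis fits one ANCOVA with treatment cohort as a class variable and refers to a single placebo cohort, which suggests pooling. On that reading power stays at 80% or above in every scenario.
- *That a planned mortality comparison loses precision.* The protocol plans counts, proportions and Kaplan-Meier curves by cohort, with no between-group interval.

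The sample size is also described as feasibility-based, with no primary efficacy endpoint. That makes power the lesser issue. It does not excuse the mismatch in group sizes.

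**Conclusion.** The contradiction is real and follows from simple arithmetic. A 4:1 third list cannot deliver the stated design. It gives 80 patients with 20 on placebo, or 95 patients with 23 on placebo and 32 rather than 20 on 125 mg.

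The harm is to the stated group sizes, to the total of 35 placebo patients, and above all to the concurrent control at the highest dose, which falls from 20 to 5 or 8. If placebo is pooled, the pooled group would then consist mostly of patients from earlier steps.

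The effect on power depends on the control group: a fall to 42% or 62% against step-3 placebo alone, but 80% or 91% against pooled placebo, where the design gives 89%. These figures take the difference, SD and t-test of {14} as given, assume that all randomised patients are evaluable, and for the pooled case assume no drift in placebo patients between steps. The article does not show which list was implemented, so no conclusion about actual allocation can be drawn.

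**What to change.** Reconcile the third list in Sequence generation {16a} with Trial design {8} and Sample size {14}. Only 1:1 in step 3 reproduces the document's own 20 and 20, 35 placebo and 95 in all.

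Before step 3 opens, have the independent statistician who communicates with the DSMB confirm the ratio of the list held in the web response system. That person is outside the management and conduct of the study, so the check need not unblind the trial team.

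If step 3 has already been randomised at 4:1, restate the group sizes, the placebo total, the overall sample size if it changes, and the basis of the power statement, including whether the comparison uses step-3 placebo or placebo pooled over steps.

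The cost is one line in the protocol and a check of one list, with no patients beyond the 95 already planned.

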## Introduction

### Background and rationale {6a}

#### Acute respiratory distress syndrome (ARDS)

ARDS is a common pathology seen in intensive care units globally, with associated significant mortality and even long-term morbidity. ARDS is a clinical diagnosis accounting for up to 20% of unplanned ICU admissions. Mortality in ARDS patients is still high. The LUNG SAFE study [Belani2016] reports a hospital mortality of 40%, with a significant increase across the ARDS severity categories, in line with Berlin definition (34.9%, in mild ARDS; 40.3% in moderate ARDS; 46.1% in severe ARDS). The socioeconomic burden of the disease of critical illness is immense. A recent systematic review regarding the endpoint “return to work after critical illness” reported that approximately two-thirds, two-fifths, and one-third of previously employed intensive care unit survivors are jobless up to 3, 12, and 60 months following hospital discharge [1].

The most recent Berlin definition of ARDS [2] is shown in Table 1. The pathophysiology of ARDS is not completely understood. Initially, a direct pulmonary or indirect extrapulmonary insult is believed to cause a release of inflammatory mediators that promotes neutrophil accumulation in the microcirculation of the lung. Activated neutrophils migrate in large numbers across the vascular endothelial and alveolar epithelial surfaces and release proteases, cytokines, and reactive oxygen species (ROS). The migration and mediator release of neutrophils lead to pathologic vascular permeability, gaps in the alveolar epithelial barrier, and necrosis of type I and II alveolar cells, resulting in pulmonary edema, hyaline membrane formation, loss of surfactant and ultimately alveolar collapse, ventilation/perfusion mismatch, decrease of pulmonary compliance, and altered gas exchange. Subsequent infiltration of fibroblasts can lead to collagen deposition, fibrosis, and worsening disease [3].

**Table 1 Tab1:** The Berlin definition of acute respiratory distress syndrome

Timing	Within 1 week of a known clinical insult or new or worsening respiratory symptoms
Chest imaging	Bilateral opacities—not fully explained by effusions, lobar/lung collapse or nodules ^a^
Origin of edema	Respiratory failure not fully explained by cardiac failure or fluid overload Need objective assessment (e.g., echocardiography) to exclude hydrostatic edema if no risk factor present
Oxygenation	
Mild	200 mmHg < P_aO2_/F_iO2_ ≤ 300 mmHg with PEEP or CPAP ≥ 5 cm H_2_O ^b, c^
Moderate	100 mmHg < P_aO2_/F_iO2_ ≤ 200 mmHg with PEEP ≥ 5 cm H_2_O
Severe	P_aO2_/F_iO2_ ≤ 100 mmHg with PEEP ≥ 5 cm H_2_O

Abbreviations: *CPAP*, continuous positive airway pressure; *F*_*iO2*_, fraction of inspired oxygen; *P*_*aO2*_, partial pressure of arterial oxygen; *PEEP*, positive end-expiratory pressure

^a^ Chest radiograph or computed tomography scan

^b^ If altitude is higher than 1000 m, the correction factor should be calculated as follows: [P_aO2_/F_iO2_ × (barometric pressure/760)]

^c^ This may be delivered noninvasively in the mild acute respiratory distress syndrome group

Most cases of ARDS in adults are associated with pulmonary sepsis (46%) or non-pulmonary sepsis (33%). Risk factors include those causing direct lung injury (e.g., pneumonia, inhalation injury, pulmonary contusion) and those causing indirect lung injury (e.g., non-pulmonary sepsis, burns, polytrauma, transfusion-related acute lung injury) [4].

ARDS is an orphan condition. The in-hospital mortality rate for ARDS is estimated to be between 34 and 55% [5]. Risk factors for mortality include older age, multiorgan dysfunction and presence of pulmonary and non-pulmonary comorbidities. Most ARDS-related deaths are due to multiorgan failure. Refractory hypoxemia accounts for only 16 percent of ARDS-related deaths [6].

Treatment of ARDS is supportive, including mechanical ventilation, prevention of stress ulcers and venous thromboembolism, nutritional support and treatment of the underlying disease. Pharmacologic options for the treatment of ARDS are limited. The use of corticosteroids is controversial; randomized controlled trials and cohort studies tend to support the early use of corticosteroids for decreasing the number of days on a ventilator; however, no consistent mortality benefit has been shown with this therapy [7, 8]. No targeted pharmacological treatment of patients with pulmonary permeability edema in ARDS is currently available, and therefore, new therapeutic approaches are warranted.

### Solnatide (INN, laboratory code AP301)—background and pre-clinical studies

Solnatide (AP301) is a synthetic peptide composed of 17 natural amino acids (Cys–Gly–Gln–Arg–Glu–Thr–Pro–Glu–Gly–Ala–Glu–Ala–LysPro–Trp–Tyr–Cys) with a molecular mass of about 2000 Da. Basically, solnatide is a circularized presentation of the lectin-like domain (so called TIP domain) of human TNF-α. Solnatide lacks any known pro-inflammatory activity to TNF-α. The Investigational Medicinal Product (IMP) “Solnatide 25 mg powder for reconstitution for solution for inhalation” is a sterile, lyophilized preparation of solnatide and contains no additional ingredients. The clinical route of administration is pulmonary delivery by inhalation of a liquid aerosol.

Pharmacological studies using rodent models have indicated that solnatide is an important regulator of alveolar fluid balance in healthy and injured lungs. Intratracheally and pulmonary-administered solnatide improved alveolar liquid clearance (ALC) in in situ flooded mouse lungs, in ex vivo models of flooded rat lungs, and in rat lungs prior to transplantation [9–11]. In a porcine bronchoalveolar lavage model of ARDS, inhalation of nebulized solnatide resulted in an increased P_a_O_2_ /F_i_O_2_ ratio and reduced extravascular lung water (EVLW) [12].

The alveolar fluid clearing capacity of solnatide is related to activation of the amiloride-sensitive sodium channel (ENaC), the major driving force for reabsorption of water through the alveolar epithelium [13–17]. ENaC is responsible for the maintenance of Na^+^ balance, extracellular fluid volume, and blood pressure and is located at the apical membrane of salt-reabsorbing tight epithelia of the distal nephron, the distal colon, salivary and sweat glands, and the lung, where it constitutes the rate-limiting step for vectorial movement of Na^+^ ions from the luminal side into the cell interior. The basolaterally located Na-K-ATPase actively transports Na^+^ out of the cell, providing the driving force for Na^+^ reabsorption. In the lung, Na^+^ transport through apically located ENaC in the alveolar epithelium is crucial for maintaining the correct composition and volume of alveolar lining fluid, enabling optimal gas exchange [18, 19]. Disruption of these processes occurs in pathologies in which permeability of the alveolar epithelium and pulmonary capillary endothelium is increased, leading to excessive accumulation of alveolar fluid and edema [20].

In addition to its ALC activity, solnatide inhibits hypoxia-induced reactive oxygen species (ROS) production and counteracts various ROS and toxin-mediated effects: solnatide inhibits protein kinase C (PKC) alpha activation thereby restoring ENaC activity. Solnatide reduces the degree of myosin light chain (MLC) phosphorylation and thus protects and restores the barrier integrity of endothelial and epithelial cells [21]. Solnatide lacks pro-inflammatory activity and does not lead to an increased production of chemokines or an increased infiltration of neutrophils in rat lungs upon intratracheal instillation.

The standard battery of safety pharmacology studies did not reveal drug-related adverse effects in any of the animal models. From animal studies in various species (rodent and non-rodent), it is evident that peptide clearance from blood is quite fast (decrease by a magnitude of 3 orders within 2 h) after bolus intravenous injection of 25 mg solnatide/kg BW. In the 14-day toxicity study in the rat, lung tissue samples were taken after the last treatment on day 14 and analyzed for the presence of solnatide; no test item was detected in lung tissue approximately 30, 60, and 90 min after the end of treatment in the low-, mid-, and high-dose group respectively.

